## 1. Protocol summary

### **Title: Surgery on the aortic arch and feasibility of EEG (SAFE) monitoring**

**Population:** Target population is all neonates ( $\leq 4$  weeks corrected age) requiring aortic arch surgery at Birmingham Children's Hospital (BCH).

**Study duration:** Participants are enrolled at one time point and provide electroencephalography (EEG) data for analysis and use in future research projects. The study will finish September 2028.

**Aim:** To identify if EEG monitoring can be used to optimise neuroprotection perioperatively and therefore contribute to risk reduction. We will do this by tracking temperature-dependent changes in brain electrical activity during cooling to 18 degrees Celsius (the temperature used by BCH team) in neonates undergoing aortic arch repair, and identify the temperature at which electro-cerebral inactivity (ECI) is achieved. Pre- and Post-operative EEG will be recorded to identify groups which require increased perioperative resource.

**Primary objective:** To evaluate whether the temperature at which ECI on EEG is achieved is a modifiable risk factor associated with the long-term neurodevelopmental outcomes of neonates undergoing aortic arch surgery with deep hypothermic circulatory arrest (DHCA).

**Secondary objectives:** To report perioperative EEG patterns, seizure burden, and neurodevelopmental outcome in this previously unmonitored group.

**Funding:** HEE/NIHR Doctoral Clinical and Practitioner Academic Fellowship (NIHR302896) awarded to [name] (2023-2026). The follow-up sub-study is funded by a research grant from Birmingham Women's and Children's Hospital Charity (37-6-206).

**Schematic of study design:** Patients scheduled for aortic arch repair will be identified from the surgical waiting list by the Principal Investigator (PI) and communicated to the research team via a secure messaging app (eg. WhatsApp). A Parent Information Sheet will be provided to the parent or guardian of potential study participants, and they will be asked to give written informed consent for their child to participate (Figure 1). Neurophysiology will complete a case report form (CRF), apply electrodes to the scalp, synchronize EEG to internal clock of IntelliVue X3®, and acquire EEG. After surgery, EEG electrodes will be transferred to a paediatric intensive care unit (PICU) cerebral function analysing monitor (CFAM) for 24 hours of postoperative EEG acquisition. The Chief Investigator (CI) and PI will analyse EEG and temperature data. Routinely collected clinical and surgical variables will be recorded by the PI.

**Follow-up:** With consent, the parents or guardians of participants enrolled in the study will be re-approached 22-26 months following surgery to participate in the SAFE-Follow-up of Infant Neurodevelopment (SAFE-FIN) sub-study. With additional consent, neurodevelopmental outcome will be assessed by a trained physiotherapist using the Bayley-III scale of infant development (see Appendix).

[figure not shown]

Figure 1: The flow of participants through the SAFE study.

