## 5. Outcomes measures

### i. Primary outcome

The proportion of participants who achieve ECI during cooling before the start of DHCA, and in these, the temperature (degrees Celsius) and variability ( $\pm$ SD) at which ECI is achieved.

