### ii. Secondary outcomes

- The relationship between whether or not ECI is achieved during cooling before DHCA and clinical outcome measures.
- The duration of ECI (minutes) and its relationship with clinical outcome measures.
- The morphology, amplitude and continuity of EEG activity during hypothermia, DHCA, selective antegrade cerebral perfusion (SACP) and rewarming to normothermia.
- Pre- and postoperative background EEG patterns and seizure burden (absent, present, status epilepticus). This will be assessed retrospectively by specialist clinical neurophysiologists, with reference to published articles.

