## 8. Statistical analysis

Baseline and procedural characteristics will be summarized using median with interquartile ranges, or mean with standard deviation for continuous variables, and counts with percentages for categorical variables. Study feasibility will be measured by counts and percentages of successful patient recruitment,

data collection procedures and technically successful EEG recordings. The temperature (degrees Celsius) and variability ( $\pm$ SD) at which ECI is achieved and evolution of continuity will inform EEG utility in cardiac surgery. Secondary analysis will compare demographic, clinical and EEG variables between those with ECI at DHCA and those without to identify subgroups which may require increased neurocritical care resource.

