**Appendix: SAFE-Follow-up assessment of Infant Neurodevelopment (SAFE-FIN) sub-study**

**Population:** All neonates ( $\leq 4$  weeks corrected age) recruited to the SAFE Monitoring study at BCH in whom consent for future contact for determining development was obtained.

**Study duration:** With consent, the parents or guardians of participants will be re-approached at 22-26 months following surgery for a single assessment of neurodevelopment.

**Aims:** To 1) identify whether perioperative EEG activity is associated with long-term neurodevelopmental outcome, 2) assess feasibility of conducting follow-up neurodevelopmental assessments in this population.

**Primary objective:** Assess neurodevelopmental outcome following aortic arch surgery in neonates approximately 24 months post procedure using the Bayley-III scale of infant development.

**Secondary objectives:** Evaluate whether the duration of electrocerebral inactivity (ECI), or not achieving ECI prior to deep hypothermic circulatory arrest (DHCA); seizure burden and other EEG patterns are associated with Bayley-III scores. We will also determine whether late follow-up neurodevelopmental assessments are feasible in this population.

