**Secondary outcomes:** The scaled and standard score, including percentile rank and age-equivalent for Language, Cognitive, Motor, and Social-Emotional Bayley-III domains. Number of participants recruited to follow-up assessment.

**Analysis:** Scores for each domain and subtest will be summarized using mean and standard deviation.

[figure not shown]

Figure 3: Participant flow through the sub-study

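### The primary objective ties temperature at ECI to long-term neurodevelopment, but no stated outcome or analysis links the two and the sample size does not address the question

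*Protocol*

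**What the plan says.** Section 1 gives the primary objective as "To evaluate whether the temperature at which ECI on EEG is achieved is a modifiable risk factor associated with the long-term neurodevelopmental outcomes", and section 2.ii repeats it as objective 1. The exposure is temperature at ECI and the endpoint is neurodevelopment.

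Section 5.i defines the primary outcome as "The proportion of participants who achieve ECI during cooling before the start of DHCA, and in these, the temperature (degrees Celsius) and variability". Section 5.ii adds two relationships: "The relationship between whether or not ECI is achieved during cooling before DHCA and clinical outcome measures" and "The duration of ECI (minutes) and its relationship with clinical outcome measures".

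Section 7 projects 41 ECI achievers among 74 recruits and gives the expected precision of their mean temperature. It treats the secondary outcomes as exploratory. Section 8 plans baseline summaries, feasibility counts, a description of temperature at ECI, and a comparison of children with and without ECI.

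Bayley-III belongs to the SAFE-FIN sub-study, which needs further consent (section 6 and Appendix). Its secondary objective begins "Evaluate whether the duration of electrocerebral inactivity (ECI), or not achieving ECI prior to deep hypothermic circulatory arrest (DHCA" and goes on to seizure burden and other EEG patterns. Its primary outcome is the adaptive behaviour score. Its stated analysis is "Scores for each domain and subtest will be summarized using mean and standard deviation".

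**The concern.** A primary objective should lead to an outcome that measures it and a sample size chosen for it. Here the objective is an association, while the primary outcome and sample size concern a proportion and a mean. The neurodevelopmental endpoint sits in an optional sub-study, and the exposures listed there leave out the one that the primary objective names.

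What is at stake is what the study may claim. A statement at the end about ECI temperature and neurodevelopment would carry the status of a primary finding. It would rest on an analysis the protocol does not describe, in children who both reached ECI and returned for assessment, with no stated power. The word modifiable adds a causal claim that the design does not test.

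**Working it through.** **Step 1. Trace the objective through the protocol.**

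| Place | ECI measure | Neurodevelopment? | Link to ECI temperature? |
|---|---|---|---|
| Sections 1 and 2.ii, primary objective | Temperature at ECI | Yes | Yes |
| Section 5.i, primary outcome | Proportion with ECI; temperature at ECI | No | No |
| Section 5.ii, secondary outcomes | ECI achieved or not; ECI duration | Not named (clinical outcome measures, undefined) | No |
| Section 7, sample size | Mean temperature at ECI | No | No |
| Section 8, analysis | Temperature described; ECI versus no ECI compared | Not named | No |
| Appendix, secondary objective | ECI duration; ECI not achieved; seizure burden; other EEG patterns | Yes (Bayley-III) | Not named |
| Appendix, analysis | None | Yes (mean and SD of scores) | No |

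The link appears only in the objective itself.

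**Step 2. Reproduce the stated sample size.** Inputs from section 7: 17/30 reaching ECI, SD 2.9°C, 74 recruited, 41 with ECI.

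- Rate: 17/30 = 56.7% (printed as 56%). 74 × 0.56 = 41.4 and 74 × 17/30 = 41.9, so 41 is consistent.
- Half-width = 1.96 × SD/√n = 1.96 × 2.9/√41 = 0.89°C. With the t quantile it is 0.92°C. Both round to 0.9.

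The figure is right for what it targets, the precision of a mean temperature. It contains no neurodevelopmental effect size, no power and no allowance for loss to follow-up.

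**Step 3. What that sample could detect for the association (illustration only).** Assumptions not in the protocol: ECI achievers only, unadjusted correlation of ECI temperature with one Bayley-III score, two-sided 5%, 80% power, follow-up between 100% and 60%.

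Smallest detectable r = tanh((1.960 + 0.842)/√(n − 3)).

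| Assumed follow-up | n of 41 | Smallest detectable r | Power if r = 0.3 |
|---|---|---|---|
| 100% | 41 | 0.43 | 48% |
| 80% | 33 | 0.47 | 40% |
| 70% | 29 | 0.50 | 35% |
| 60% | 25 | 0.54 | 31% |

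In the other direction, n = ((1.960 + 0.842)/atanh(r))² + 3. For r = 0.3 this gives 85 children with both measurements, and 85/(17/30) = 150 recruited even with complete follow-up.

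These figures do not apply to a model that keeps in the projected 74 − 41 = 33 children without ECI, because their exposure would have to enter in some other form.

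**Step 4. The word modifiable.** Section 2.iii says the study procedures do not change how patients are managed. Temperature at ECI is therefore observed, not set by the study. It varies between children (SD 2.9°C), so an association can be estimated. Whether changing it would change outcome is a different question, which this design does not test.

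**The case against.** The strongest reply is that both halves of the objective are measured: ECI temperature is part of the primary outcome and Bayley-III is scheduled at 22 to 26 months. Section 6 and the Appendix also aim to relate perioperative EEG activity to neurodevelopment, which could be read to include ECI temperature. This stands as far as it goes. A reader might infer that the study cannot address its main question at all, and the documents do not support that. But where the Appendix lists its exposures, temperature is not among them, and a primary objective should not depend on a generous reading of a sub-study aim.

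A reader might also infer that the study will yield only a proportion, a mean temperature and a table of Bayley means. That is wrong too. Sections 5.ii and 8 and the Appendix plan comparisons and associations for ECI achievement and duration, and the Appendix adds seizure burden and other EEG patterns. None of these uses ECI temperature as the exposure.

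The form of any regression, and the handling of children who never reach ECI, may properly sit in a statistical analysis plan that is not shown. Their absence is not counted here. Such a plan could supply a model, but it would not remove the mismatch between the protocol's own primary objective, primary outcome and sample size.

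Finally, section 2.ii is concerned with cooling beyond the point of ECI, which gives modifiable a plausible clinical meaning. That explains the word but does not make the cohort a test of it.

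**Conclusion.** The point holds in this form: the primary objective states an association that no listed outcome or analysis takes up and that the sample size does not address. This follows from the protocol text alone. An association analysis remains feasible with the data collected, but as written it is unspecified and unsized, and it cannot establish that ECI temperature is modifiable in the causal sense.

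The range of about 0.43 to 0.54 only gives a sense of scale. It rests on the assumed follow-up, power and unadjusted achievers-only correlation in the working, and the protocol states no follow-up rate. The stated calculation of 74 recruits, 41 achievers and ±0.9°C is correct for its own purpose.

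**What to change.** - **Sections 1 and 2.ii.** Make the primary objective what section 5.i and section 7 deliver: to estimate the proportion of neonates reaching ECI before circulatory arrest and the temperature at which they reach it. State the relation of ECI temperature to neurodevelopment as an exploratory objective, worded as an association, without the modifiable risk factor claim.
- **Section 5.ii.** Cross-reference Bayley-III, since neurodevelopmental outcome is also part of the secondary objectives.
- **Appendix, secondary objectives.** Add temperature at ECI to the exposures and relate it to the sub-study's existing primary score, adaptive behaviour.
- **Section 7.** State that the sample size gives precision for mean temperature and does not power the neurodevelopmental association. If a detectable correlation is quoted, label it as achievers only and give the assumed follow-up.

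The cost is a wording amendment, with no new patients or data. The downside is a less ambitious headline objective.

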## 2. Background

### i. Introduction

Aortic arch repair is a complex operation which requires specialised neuroprotective strategies when arteries supplying the brain with blood are temporarily occluded during the repair. Reducing cerebral metabolism via hypothermia protects against the effects of cortical ischaemia and optimal cerebral protection is thought to occur during periods of electro-cerebral inactivity (ECI) as measured via EEG.

ECI, defined as  $<2\mu\text{V}$  EEG activity for a 3-minute period, occurs at core temperatures between  $28-12^{\circ}\text{C}$ . Sixty percent of adults achieve ECI at  $18^{\circ}\text{C}$ , the temperature used by the BCH team, but recent data in infants suggests more variability. Without EEG, multisite temperature monitoring is recommended to ensure adequate brain cooling (class 1 recommendation, level B evidence) but time to ECI, and cortical temperature, are not precisely predictable from oesophageal or nasopharyngeal temperature (temperature monitors used at BCH).

Up to 20% of potential study participants will develop sub-clinical seizures perioperatively, and the only way to detect these is via EEG. Preoperative EEG may help identify which patients are more likely to require specialized neuroprotection as certain patterns will highlight central nervous system abnormalities. Although there is currently insufficient evidence to support routine EEG monitoring for the study population in question it is feasible that:

- Preoperative EEG could identify patients at high risk of neurological complications.
- There may be inter-individual variation in the degree of hypothermia required to achieve ECI, and thereby optimal neuroprotection.
- Postoperatively, a substantial proportion of patients may develop subclinical seizures which go undetected in the absence of EEG monitoring and are associated with adverse neurological outcome.

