### **iii. Potential benefits and risks**

#### **Known potential benefits**

EEG interpretation may have clinical significance to the participant's care. Seizures, epileptiform activity, immaturity, evidence of hypoxic ischaemic encephalopathy (HIE), and Bayley-III scores will be disclosed to the clinical team looking after the participant. By improving our understanding of optimal neuroprotection during surgery, this study has the potential to improve the outcomes of future patients undergoing aortic arch repair.

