##### ii. Clinical data collection

Participants’ CRF will be entered onto a secure electronic database within Birmingham Children’s Hospital (BCH). Offline/hard copies of CRFs will be stored within a research master site file located within the neurophysiology department of BCH. The CRF will be populated by the PI. Other routinely collected clinical variables will be obtained from the cardiac database. Research collaborators from the Neurophysiology department will assess pre- and postoperative EEG and seizure burden in accordance with previously published guidelines.

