**Schematic of study design:** Participant flow through the sub-study is shown in figure 3. The PI will inform physiotherapy when neonatal SAFE Monitoring study patients are approaching the 24-month post procedure time point. The PI will agree several dates and times when the assessment could take place with physiotherapy and neurophysiology. The PI will then contact the families of recruited neonates and ask whether they would be interested in attending a follow-up appointment to assess their child's development. Where possible, these will be arranged in-line with BCH outpatient clinic appointments to reduce the burden on the family. The PI will confirm the appointment date and time with the parent or guardian and inform physiotherapy. All assessments will take place in the department of neurophysiology. The parent or guardian has already given written informed consent to be contacted about a follow-up assessment of their child's development. Physiotherapy will perform the Bayley-III assessment and document results on a dedicated score sheet. After the assessment, the physiotherapy team will email the PI the results of the assessment and provide the PI with the original hard copy for the site file. Bayley-III results will be shared with the child's consultant Paediatrician.

**Procedures:** All participants will be assessed using the third edition of the Bayley Scales of Infant and Toddler Development (Bayley-III) by a trained physiotherapist. This scale is an individually administered instrument that assesses developmental functioning of children between 1 month and 42 months of age. It is used to identify suspected delay in children consistent with current academia pertaining to child development. It can also assist paediatricians with intervention planning and other important clinical services. Additionally, the Bayley-III is designed to promote an understanding of the child's strengths and weaknesses in relation to five developmental domains: cognitive, language, motor, social-emotional, and adaptive behaviour. We anticipate the assessment appointment will last approximately 90 minutes, with an additional 90 minutes for analysis and interpretation of findings after the appointment.

**Primary outcome:** Adaptive behaviour score with percentile rank.

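### The protocol does not require ECI to be marked without sight of temperature and outcome, or the Bayley-III assessor to be unaware of EEG findings, so the EEG-outcome associations are open to observer bias

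*Protocol*

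**What the plan says.** **Who handles the data.** The study schematic in the Protocol summary (section 1) says that "The Chief Investigator (CI) and PI will analyse EEG and temperature data", and then that "Routinely collected clinical and surgical variables will be recorded by the PI". Section 4.ii has the PI populate the CRF and adds that "Other routinely collected clinical variables will be obtained from the cardiac database". Section 10.i gives the PI access to the monitor data through PICU collaborators.

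**What is measured.** The primary outcome (section 5.i) is "The proportion of participants who achieve ECI during cooling before the start of DHCA, and in these, the temperature (degrees Celsius) and variability". Section 2.i defines ECI as activity below 2 µV lasting 3 minutes. No section says how that limit is read from the recording, on which channels, or by how many readers. Section 5.ii assigns retrospective specialist reading to the pre- and postoperative patterns and seizure burden. It does not extend this to the intraoperative ECI mark.

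**What is tested.** Section 5.ii lists "The relationship between whether or not ECI is achieved during cooling before DHCA and clinical outcome measures", and a matching item for ECI duration. The SAFE-FIN Appendix tests ECI duration, failure to reach ECI, seizure burden and other EEG patterns against Bayley-III scores.

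**Who assesses development.** A trained physiotherapist does so. The Appendix says that "The PI will inform physiotherapy when neonatal SAFE Monitoring study patients are approaching the 24-month post procedure time point". The PI also arranges the appointment, which is held in the neurophysiology department, and is sent the results.

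**What is released.** Under section 2.iii, seizures, epileptiform activity, immaturity and evidence of HIE "will be disclosed to the clinical team looking after the participant". Section 9 repeats this list.

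**The concern.** One person, the PI, holds the exposure data (EEG and temperature), the clinical data and the developmental scores, and no order of work keeps them apart. The protocol also tells its readers what to expect: section 2.ii cites a report that cooling beyond ECI predicts poor neurodevelopment. If an ECI onset or offset is placed by someone who knows the temperature or how the child fared, ECI status, duration and temperature can drift towards the expected pattern.

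The same applies at the other end. A physiotherapist who has learned that a child had seizures may score that child differently. Seizure burden is both an exposure under test and a finding that the protocol deliberately releases. Either route could create or exaggerate the associations that the primary objective (section 1) and the SAFE-FIN secondary objectives set out to examine. Error of this kind is systematic, so recruiting more infants does not reduce it.

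**Working it through.** **1. Reproduce the plan's own figures (section 7).** Inputs: 17 of 30 reached ECI, SD 2.9 °C, 74 to be recruited, 41 expected to reach ECI, half-width ±0.9 °C.
- Expected number with ECI: 74 × 0.56 = 41.4, or 74 × 17/30 = 41.9. Stated: 41.
- Half-width of the 95% interval for the mean: 1.96 × 2.9 / √41 = 0.89 °C. With the t quantile it is 0.92 °C. Stated: 0.9 °C.

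The plan's figures reproduce, and this point changes none of them.

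**2. Look for masking at each step.**

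| Step | Who does it | Masking stated |
|---|---|---|
| Analysis of EEG and temperature, the basis for ECI (sections 1, 5.i) | CI and PI | None |
| Clinical variables (sections 1, 4.ii) | PI; some from the cardiac database | None |
| Pre- and postoperative EEG, seizure burden (sections 4.ii, 5.ii) | Neurophysiology specialists, retrospectively | None |
| Arranging Bayley-III and receiving its results (Appendix) | PI | None |
| Bayley-III scoring (Appendix) | Physiotherapist | None |

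The roles are partly separated. No statement says what any reader or assessor may know, or in which order the work is done.

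**3. How far could reading error move the mean temperature?** The documents give no reader error, so these shifts are assumptions.
- The same shift b in all 41 patients moves the mean by b. Relative to the half-width of 0.89 °C: 0.25/0.89 = 28%, 0.5/0.89 = 56%, 1.0/0.89 = 113%.
- A shift of 1 °C in one patient moves the mean by 1/41 = 0.024 °C, which is negligible.

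**4. How far could it move the proportion?** One changed ECI status moves it by 1/74 = 1.4 percentage points. The sampling half-width at 17/30 with 74 infants is 1.96 × √(0.567 × 0.433 / 74) = 0.113, about 11 points. A single changed status is small against that.

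**5. Associations.** No arithmetic is possible here, because the size depends on how strongly the reading or scoring follows knowledge of the other variable, and the documents give nothing on that. Only the direction of reasoning can be shown: such error is tied to outcome or exposure, so it biases the association and is not absorbed into a wider interval.

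**The case against.** The strongest reply is that this is an observational study focused mainly on estimation, with an ECI definition that is numerical, roles that are partly split, and no demonstrated error. Much of that stands, and it rules out several stronger readings that a reader might infer.

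- **That ECI is judged by eye on a noisy trace, with temperature alongside.** The protocol says neither. EEG and temperature are recorded on separate devices linked by a clock, and it is not stated whether temperature is visible when ECI is marked. The threshold limits discretion. It does not remove it, because no reading method is given.
- **That both investigators record the clinical outcomes.** Only the PI is said to do so. The variables are routinely collected, partly from the cardiac database, so biased recording is the weakest route.
- **That the physiotherapist will be told ECI results.** ECI status, duration and temperature are not on the disclosure list, and the PI is said to notify and schedule, not to pass on EEG findings. Unmasking on ECI is possible but not stated. It is more plausible for seizures, which are released to the clinical team.
- **That displacing one patient's mark rivals the whole confidence interval.** The ±0.9 °C belongs to a mean of 41, so one patient's shift is negligible, as shown above.
- **That readers are drawn towards the 18 °C target.** The feasibility mean of 22.6 °C lies 4.6 °C above it, and the documents contain no evidence of such a pull.

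The unseen SAP is not an answer. Who reads what, in which order, and what an assessor may know are matters of study conduct, which this protocol already assigns by role.

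**Conclusion.** The point holds in a limited form. The protocol leaves the ECI marks unprotected from knowledge of temperature and outcome, and the Bayley-III scores unprotected from knowledge of EEG findings, while making the association between them an objective. The main exposure is in those associations, most plausibly through seizure findings known to the assessor and through ECI marks made after outcomes are known. The effect on the mean temperature is of concern only if a shift is systematic: at an assumed 0.5 °C in all patients it would take up about 56% of the planned half-width. That figure is an illustration, not an estimate. Nothing in the documents shows that bias has occurred. The sponsor should make the change because it is cheap and because sample size cannot repair the problem afterwards.

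**What to change.** **Sections 4.i and 4.ii.** State that ECI onset and offset are marked from the stored, coded EEG alone, with the temperature trend hidden, before clinical outcomes are abstracted and before any Bayley-III score is received. Lock the marks, then merge temperature using the synchronised clock. Say in the same place how the 2 µV limit is measured.

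**Appendix.** State that the physiotherapist receives no EEG, ECI or seizure information until scoring is complete.

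**Cost.** A changed order of work and a few sentences of protocol. Existing staff can do it; no extra reader is needed and no sample size figure changes. If the 30 feasibility patients count towards the 74, which section 7 does not make clear, their stored recordings would need to be re-marked in the same way. Where outcomes are already known to the reader, the masking will be weaker. Masking of the physiotherapist cannot be guaranteed, since seizures may be known to the child's clinical team or family.
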